### Participant flow

The number of participants screened, included, randomized, withdrawn, and lost to follow-up will be summarized in the analyses.

### Baseline comparability of the study groups

Baseline data will be summarized by arm. Categorical variable data will be summarized by number and percentage per category. The synthesis of continuous variables will be performed using the mean and standard deviation for approximately normally distributed variables. For variables that are not normally distributed, the median and interquartile ranges will be used. At this point, no formal statistical testing will be performed because differences between study arms are more likely to be the result of chance than the consequence of randomization.

#### Study outcomes

##### Primary outcome

The primary outcome will be the assessment of asymptomatic/symptomatic malaria status and the parasite density of *P. falciparum* during pregnancy at every visit for every participant. The asymptomatic malaria status is defined as the presence of *P. falciparum* diagnosed by an us-RDT in the peripheral blood and a T°<37.5°C; symptomatic malaria is defined as the presence of *P. falciparum* diagnosed by an us-RDT in the peripheral blood and temperature and/or a history of temperature T°≥37.5°C. The parasite density is assessed by the quantification of *P. falciparum* parasites in the peripheral blood of participants by a thin blood smear examined by standard malaria microscopy.

##### Secondary outcomes

During the pregnancy, the anemia status and the incidence of spontaneous abortions or intrauterine deaths will be evaluated in each visit for every study participant. Anemia is assessed as a level of hemoglobin (Hb) <11g/dl. The spontaneous abortion is the loss of pregnancy naturally before 20 weeks of gestation. Intrauterine death refers to the loss of pregnancy after 20 weeks of gestation.

At birth, for the offspring, the neonatal, the early neonatal, and the neonatal morbidity will be assessed. The neonatal morbidity is estimated at birth and refers to any of the following: reterm birth (birth before 37 weeks of gestation), low birth weight (birth weight under 2500 g), and small for age. Early neonatal and neonatal morbidities will be assessed respectively as infant death at birth or within 7 days of life and infant death within the first 28 days of life.

### Interim analyses

Not applicable. The non-inferiority of ISTp-US-Py compared to IPTp-SP will be assessed after the follow-up period of the last participant.

### Methods for additional analyses (e.g., subgroup analyses) {20b}

Not applicable. The aim of this study will be to assess the non-inferiority of ISTp-US-Py compared to IPTp-SP. We will carry out the evaluation by comparing the performance of ISTp-US-Py and IPTp-SP. No sub-group analysis will be performed.

### Methods in analysis to handle protocol non-adherence and any statistical methods to handle missing data {20c}

For each variable, statistical tests will be performed with the available data. A 10% sample size adjustment will be made to ensure adequate power despite the loss to follow-up of some participants.

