#### Outcomes {12}

##### Primary outcome

The primary outcome will be the assessment of the malaria status over the pregnancy at every visit for each study participant.

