### Recruitment {15}

Based on the assumption described above, a total of two hundred and twenty pregnant women is the minimal sample size required to answer our research question. However, anticipating on a non-compliance and/or loss-to-follow-up rate of 10%, the adjusted total sample size required will be 242 pregnant women (121 participants per arm).

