### Plans to promote participant retention and complete follow-up {18b}

Participant’s visits are scheduled on monthly basis. In case of a missing visit, the site clinicians will be in charge to phone the participants to enquire for the reason of the missing visit and encourage them to come to the study site. In case participants cannot be reached by phone, a community health worker will be visiting the households for enquiring and encourage participants to come to the study site. In case participants are not reachable, they will be considered as lost to follow-up after 3 missing visits and all attempts to reach out to them will be documented.

In case of loss to follow-up, all the data collected during the woman participation in the study will be used for the analysis. However, in case of consent withdrawal, the participant data will not be used for the analysis.

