## Statistical methods

### Statistical methods for primary and secondary outcomes {20a}

#### General analysis principles

Data analysis will be performed after the end of the follow-up period of the last participant included in the study.

Study participants will receive two different interventions depending on which group they are enrolled in. The first group will undergo intermittent screening during pregnancy using ultra-sensitive malaria rapid diagnostic test and treatment with pyronaridine-artesunate—Pyramax® (ISTp-US-Py), and the second group will receive an intermittent preventive treatment as suggested by the NMCP. The analysis will mainly compare the two groups to assess the outcomes of the study. All AEs (severe or non-severe) will be reported in the trial publication and compared in the study arms and gestational weeks. To assess the effect of the study interventions in the IPT and the ISTp arms, we will use the intention-to-treat approach. Meaning that all the participant who has been randomized to an arm or another will be considered as part of that arm for the analysis despite their level of completion.

Data from every woman included with baseline and at least one further visit will be analyzed in the treatment arms to which they were assigned. Safety data from all participants who received at least one dose of the study drug will be used in the analysis to describe AEs. AEs will be grouped by treatment group for the number of events and number of participants with type of event. Descriptive statistics will be summarized by treatment arm and visits.

For all statistics, the confidence intervals will be two-sided and at the 95% level, and the value of *p* < 0.05 will be interpreted as statistically significant.

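### The available-data rule for malaria gives a non-inferiority comparison no protection against loss that differs by arm or is related to infection; the effect is small unless loss is clearly unequal or informative

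*Protocol article*

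**What the plan says.** The section on non-adherence and missing data {20c} makes two statements. The first is the rule: "For each variable, statistical tests will be performed with the available data". The second is its only other measure: "A 10% sample size adjustment will be made to ensure adequate power despite the loss to follow-up of some participants". The Recruitment section {15} gives the same allowance: "anticipating on a non-compliance and/or loss-to-follow-up rate of 10%, the adjusted total sample size required will be 242 pregnant women".

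Two other sections decide whose data enter:
- Retention {18b}: "In case of loss to follow-up, all the data collected during the woman participation in the study will be used for the analysis". For withdrawal, however, "in case of consent withdrawal, the participant data will not be used for the analysis".
- General analysis principles {20a}: "Data from every woman included with baseline and at least one further visit will be analyzed", in the assigned arm and whatever the degree of completion.

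The primary outcome is "the assessment of the malaria status over the pregnancy at every visit for each study participant". Neither the Outcomes section {12} nor the outcome definitions under Statistical methods say how the visits combine into one result per woman. The main objective speaks of a proportion, and Table 2 sizes malaria infection as a binary outcome (18.9% IPTp, 23.4% IST). Table 1 lists monthly malaria tests at M1 to M6, with further tests at allocation and delivery.

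**The concern.** Malaria here is found by repeated testing, so a woman who is tested less often has fewer chances to be found positive. If the result is one ever/never status per woman and only existing tests are used, missed tests can lower the observed proportion but never raise it. In a superiority trial this often dilutes an effect. In a non-inferiority trial, fewer tests in the new arm make that arm look better and move the result towards the conclusion the trial seeks.

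Enrolling 10% more women restores numbers but does not remove such a bias. The trial is open label, so attendance could differ between arms. The stated rule has no safeguard for that, and the article describes no sensitivity analysis that would show whether the conclusion depends on the missing tests.

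**Working it through.** **The plan's own figures.** 220 × 1.10 = 242, or 121 per arm, as stated. The malaria row of Table 2 (total 196) reproduces as a two-arm non-inferiority calculation for one binary proportion, with a 10-point margin, one-sided 5% and 80% power: 2 × (1.645 + 0.842)² × (0.189 × 0.811 + 0.234 × 0.766) / (0.10 + 0.045)² = 195.6. This matters here only because the row was sized as a single proportion. The plus sign in the denominator, that is, the direction in which the rates were entered, is a separate matter.

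**Inputs.** The rates of 18.9% and 23.4% come from Table 2, and six monthly tests (M1 to M6) from Table 1. The following are assumptions:
- the Table 2 rates are cumulative per woman over six tests;
- per-visit risk is constant and visits are independent;
- lost women have the same underlying risk as others and leave after one or two tests;
- a woman with no positive test counts as malaria-free.

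**Formulas.** The chance of detection in k of 6 tests is 1 − (1 − p)^(k/6). With a fraction m lost after k tests, the observed proportion is (1 − m)·p + m·[1 − (1 − p)^(k/6)].

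- IPTp, p = 18.9%: one test detects 3.4%, two tests 6.7%.
- ISTp, p = 23.4%: one test detects 4.3%, two tests 8.5%.

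Example, 15% lost in ISTp and 5% in IPTp, one test each:
- ISTp: 0.85 × 23.4 + 0.15 × 4.35 = 20.5%
- IPTp: 0.95 × 18.9 + 0.05 × 3.43 = 18.1%
- Observed difference 2.4 points, against a true 4.5.

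| Loss ISTp / IPTp | Observed difference, 1 test | Observed difference, 2 tests | Points hidden |
|---|---|---|---|
| 10% / 10% | 4.1 | 4.2 | 0.3-0.4 |
| 15% / 5% | 2.4 | 2.9 | 1.6-2.1 |
| 20% / 0% | 0.7 | 1.5 | 3.0-3.8 |
| 5% / 15% | 5.9 | 5.6 | none; overstated by 1.1-1.4 |

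**At the margin.** With ISTp truly 10 points worse (28.9% against 18.9%), the first three rows hide 0.6-0.8, 2.1-2.7 and 3.6-4.7 points.

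**Effect on the error rate.** With 121 per arm, the standard error is √(0.189 × 0.811/121 + 0.289 × 0.711/121) = 0.0545. For a bias b, the chance of a false non-inferiority claim is Φ(b/0.0545 − z). Two hidden points raise it from 2.5% to 5.6% (z = 1.96, the two-sided 95% interval the article specifies), or from 5% to 10.1% at one-sided 5%. Four points raise it to 11.0% and 18.1%.

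**How likely is the imbalance?** A 10-point gap is about 12 of 121 women. If the loss probability is 10% in both arms, a gap of 12 or more in either direction arises by chance about 1.4% of the time. A gap that large would therefore normally mean loss related to the arm.

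**The per-visit reading.** If the analysis unit is the visit, a missed visit leaves both numerator and denominator. Loss unrelated to infection then causes no bias, and the table above does not apply. Informative loss still does. One possible route is the Eligibility section's rule that women who take an antimalarial not prescribed by the study clinician are excluded, because a woman treated elsewhere for malaria would fit it.

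**The case against.** The strongest objection is that no section says a woman with few negative tests is malaria-free. The outcome is assessed at each visit, and the article does not say whether Table 2's rates are per woman, per visit or at one time point. This stands, and the sizes above are therefore conditional.

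A reader might infer that the whole 10% expected to be lost or non-compliant would be scored malaria-free. The documents do not support that. Withdrawn women's data are not used, women taking non-study antimalarials are excluded, women with no visit after baseline fall outside the analysed set, and non-compliance need not mean a missed test. A reader might also infer that several points of the margin are likely to be lost, or that loss will be greater under ISTp. The first needs nearly all loss in ISTp, or lost women at much higher risk. No section supports the second.

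Some features reduce missed detection. Missed visits trigger phone calls and home visits, the same malaria tests are done at unscheduled visits, unwell women are advised to return, and Table 1 tests the mother at delivery. An infection that persists may also be found at the next test. The rule that declares loss after three missed visits concerns women who cannot be reached. It does not say that a woman who missed two was fully followed.

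Finally, the Data management section promises a separate analysis plan, and keeping lost women in their assigned arm is sound intention-to-treat practice. Detail left to that plan would be no finding. But the article states a rule, and a plan that follows it would inherit the problem.

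**Conclusion.** The point holds in a limited form. The article fixes an available-data analysis, answers loss with numbers only, and retains women with as little as one visit after baseline. For a non-inferiority comparison of a detected outcome, that leaves loss that differs by arm or is informative without any safeguard.

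The size depends on an outcome definition the article does not give. On the per-woman reading and the stated assumptions, equal loss is close to harmless (under half a point at the planned rates). A 15%/5% split hides about 2 points, enough to roughly double the false-claim rate at the margin. Only loss confined to ISTp reaches 3 to 4 points at the planned rates. More loss in IPTp pushes the other way. On the per-visit reading, only informative loss matters. The change should be made, but nothing here shows that the trial's conclusion will be wrong.

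**What to change.** For the primary outcome, replace the available-data sentence in {20c}:

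1. State how visits combine into one malaria result per woman, or state that the analysis is per visit.
2. If it is per woman, do not score a woman with missed scheduled tests and no positive test as malaria-free. Either estimate the cumulative proportion by scheduled visit in discrete time, or multiply impute missed scheduled tests using arm, gestation and earlier results.
3. Add a tipping-point sensitivity analysis in which missed ISTp tests are positive more often than missed IPTp tests, and report the point at which non-inferiority is lost.

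The 10% allowance can stay as a provision for power. The cost is analysis work before database lock and a slightly wider confidence interval. No new data are needed, because malaria tests and treatment history are already recorded at every scheduled and unscheduled visit.

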### Plans to give access to the full protocol, participant-level data, and statistical code {31c}

The essential element of the protocol has been registered in an accessible clinical trial register clinicaltrials.gov: NCT04783051. The final results of this trial will be published in open-access journals. All the anonymized participant data will be also published as additional tables along with the publications.

### Oversight and monitoring

#### Composition of the data monitoring committee, its role, and reporting structure {21a}

The trial steering committee will be composed of independent members of the Faculty of Medicine of the University of Kinshasa who are not related to the study. The steering committee will be responsible for ensuring the progress of the trial, the compliance with the protocol, and the safety of study participants. Members will have virtual or in-person meetings to review AE reports and monitor reports at quarterly meetings.

The ULTRAPYRAPREG study is embedded in a larger PYRAPREG study (PACTR202011812241529); the Data Safety Monitoring Board (DSMB) of the PYRAPREG study will be in charge of the ULTRAPYRAPREG data monitoring.

#### Adverse event reporting and harms {22}

All AEs, both severe and non-severe, will be collected and reported in the participants’ CRF and in a database. In the event of serious AEs, the study team will report to the national ethics committee and the trial steering committee no later than 48 h after the team becomes aware of the event.

An AE will be defined as any adverse medical event in a subject, regardless of the possibility of a causal relationship. The study team will collect the AEs after the consent is signed and the participant enrolled in the study. If a participant experiences an AE after enrollment but before receiving the study intervention, the event will be reported as unrelated to the study products of investigation.

All AEs occurring after entry and before the end of the follow-up period will be recorded until the end of the AE.

A SAE is any untoward medical event that results in any of the following: life-threatening condition (i.e., immediate risk of death), severe or permanent disability, prolonged hospitalization, or significant danger as determined by the Data Safety Monitoring Board. SAEs occurring after a subject has been withdrawn from the study will not be reported unless the investigators believe the event may have been caused by a study product of investigation. Investigators will determine the relationship between an event and the study drug based on a temporal relationship to the study drug, as well as whether the event is unexpected or unexplained given the subject’s clinical course, previous medical conditions, and concomitant medications.

All AEs, both severe and non-severe, will be collected and reported in the participants’ CRF and in a database. In the event of serious AEs, the study team will report to the national ethics committee and the trial steering committee no later than 48 h after the team becomes aware of the event.

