#### Criteria for discontinuing or modifying allocated interventions {11b}

Changing the distribution of intervention is not possible in the framework of this study. In the event of an allergy or other adverse event (AE) that may impact participants’ health or that of the offspring, the participant will be removed from the study and will no longer receive the intended drug in the arm in which they were allocated.

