#### Provisions for post-trial care {30}

Coverage of care after the end of the study’s planned follow-up period is scheduled up to 28 days after delivery, though this is not a part of the study but rather for ethical reasons.

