### Participant timeline {13}

Pregnant women fulfilling the inclusion/exclusion criteria will be recruited during the ANC visit over an enrollment period of about 20 months. At every scheduled and unscheduled visit, the study team will collect vital signs, blood pressure, weight, data on the medical history since the last visit (including any treatment taken), information on any AE, and current signs and symptoms (if any). At the same time, the team will collect blood samples for malaria diagnosis (us-RDT, thick and thin blood film), Hb, and dried blood spots.

The outcome of pregnancy, birth weight, APGAR score, and maternal Hb will be collected as soon as possible after delivery. A placental blood sample will be collected for the diagnosis of malaria (thin blood film) and dried blood spots. The newborn will be examined for congenital abnormalities and will be reassessed again at day 28 (Table 1).

**Table 1 Tab1:** Time and event schedule

	Enrolment	Allocation								
Timepoint**	-t_**1**_	0	M_**1**_	M_**2**_	M_**3**_	M_**4**_	M_**5**_	M_**6**_	Delivery	4–6 weeks post-end of pregnancy

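### The SAE list does not name death, first hospital admission or congenital anomaly, and after removal for an AE later SAEs are reported only if open-label investigators suspect a study product

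*Protocol article*

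**What the plan says.** All references are to the protocol article.

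- **Definition.** Adverse event reporting and harms {22} calls an event serious if it "results in any of the following: life-threatening condition (i.e., immediate risk of death), severe or permanent disability, prolonged hospitalization, or significant danger", where the last criterion is for the DSMB to determine.
- **Expedited route.** The same section sends serious events to the national ethics committee and the trial steering committee "no later than 48 h after the team becomes aware of the event".
- **After withdrawal.** The same section adds that "SAEs occurring after a subject has been withdrawn from the study will not be reported unless the investigators believe the event may have been caused"; the cause in question is a study product.
- **Removal.** Criteria for discontinuing or modifying allocated interventions {11b} begins "In the event of an allergy or other adverse event (AE) that may impact participants’ health or that of the offspring" and goes on to say that the woman is removed from the study, as well as no longer receiving the allocated drug.
- **Newborn examination.** Participant timeline {13} states "The newborn will be examined for congenital abnormalities".
- **Outcomes.** Outcomes {12} and the Study outcomes text of the statistical section make spontaneous abortion, intrauterine death, early neonatal death and neonatal death to day 28 secondary outcomes.
- **Analysis.** General analysis principles {20a} promises an intention-to-treat analysis whatever the level of completion, and a comparison of all AEs between arms.
- **Day 28.** Provisions for post-trial care {30} describes care up to 28 days after delivery and adds "though this is not a part of the study but rather for ethical reasons".

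**The concern.** The definition decides which events reach an oversight body within two days and which wait for routine review. The gravest events this trial can produce are the death of a woman, the loss of a fetus, the death of a newborn and a birth defect. None is named in the list, although the trial plans to observe most of them. The abstract describes Pyramax® as a drug not so far in field use in pregnant women, so prompt review of these events matters.

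The second problem is what happens after removal. An AE that may affect mother or child ends a woman's participation, and from then on the default is that her SAEs are not reported. What is still reported depends on a causality judgement by staff who know her arm. At stake are the completeness of safety oversight for these women and, to a lesser degree, the fairness of the comparison of harms between arms.

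**Working it through.** No arithmetic applies: the point rests on no rate, margin or sample size. The check sets the sections side by side.

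1. **Is the list closed?** Yes. Section {22} introduces it as any one of a set of consequences, with no examples clause and no reference to a fuller list elsewhere.

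2. **What does the list cover?**

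| Event | Named as an SAE criterion in {22}? | Collected elsewhere? |
|---|---|---|
| Death of the woman | No; only a life-threatening condition | As an AE |
| Intrauterine death, abortion | No | Secondary outcomes |
| Neonatal death to day 28 | No | Secondary outcome |
| First hospital admission | No; only prolonged hospital stay | As an AE |
| Congenital anomaly | No | Newborn examination |

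   Women who need admission at entry are excluded under Eligibility criteria {10}, so any admission during follow-up is new. The hospital criterion covers this only in part. Section {22} also defines an AE as an event in a subject and does not say whether a fetus or newborn is one.

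3. **Does any other section send these events to the 48-hour route?** No. The outcome sections and the newborn examination contain no link to SAE reporting. The DSMB criterion could take in some events. However, {22} names only the ethics and steering committees as recipients, so the article does not say how an event reaches the DSMB for that decision. Section {21a} says only that the DSMB "will be in charge of the ULTRAPYRAPREG data monitoring".

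4. **What happens after removal?**
   - Under {11b}, an AE that may affect mother or child removes the woman from the study, not only from the drug.
   - Under {22}, her later SAEs are then reported only if the investigators believe a study product may have caused them.
   - Under Procedure for unblinding {17b}, the study team knows every woman's arm.
   - It follows that a later SAE judged unrelated to a product is not reported. This includes harm from failed prevention, such as malaria and its effect on the pregnancy, because that is not product toxicity.

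5. **Does this fit the analysis plan?** Not well. Section {20a} keeps every randomised woman in her arm whatever her level of completion and compares all AEs. A rule that selects later events by suspected cause, after an event-driven removal, does not supply the data for that comparison.

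6. **Is day 28 inside the study?** Section {30} says the period up to day 28 is not. Outcomes {12}, Participant timeline {13}, Plans for assessment {18a} and the Study outcomes text treat day 28 as a study assessment. Because {22} records AEs only up to the end of follow-up, the answer decides whether neonatal events fall inside the safety window.

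**The case against.** The strongest reply has four parts.

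- **Partial cover.** A life-threatening condition, prolonged hospital stay and the DSMB criterion are all listed, and most maternal and neonatal deaths would pass through a life-threatening state. This stands in part. A reader might infer that the plan means to keep deaths out of expedited reporting. Nothing in the article shows such an intent; the gap is in what the list says when applied literally.

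- **Nothing is lost while a woman is followed.** Pregnancy losses and neonatal deaths are outcomes, all AEs are recorded until they end, and the steering committee reviews AE reports at quarterly meetings. This stands. For these women the loss is the 48-hour report, not the record. The SAE list therefore does not by itself distort the comparison of harms between arms.

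- **Suspected drug harms are kept.** A reader might infer that all SAEs after withdrawal go unreported, or that the record is cut short in just those women with drug-related events. The documents support neither. Section {11b} applies to any AE that may affect health, whether drug-related or not, and {22} keeps the later events suspected to come from a study product. The AE that led to removal is itself followed to its end. What remains is the later events not attributed to a product, as judged by unblinded staff.

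- **The full protocol or a DSMB charter may say more.** This is fair for the detail of DSMB routing. Section {22} names two recipients without saying that there are no others, so the article does not establish that the DSMB receives nothing. The argument is weaker for the definition, because the article prints it as the operative one.

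The wording on post-trial care is also secondary. It concerns coverage of care, and four other places put day 28 inside the study.

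**Conclusion.** The point holds in a limited form. The printed SAE definition does not name death, first hospital admission or congenital anomaly, so applied as written these events can miss the 48-hour report. Separately, removal for an AE combined with the post-withdrawal rule means that later SAEs not attributed to a product can go unreported, which conflicts with the stated intention-to-treat and all-AE comparison.

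The size cannot be computed. The documents give no expected rates of maternal, fetal or neonatal death, of anomalies or of removal for AEs, so no count of affected events is offered. The conclusion assumes that the printed list is the one used on site and that removal from the study counts as withdrawal for {22}. If the full protocol has a wider list, or continues follow-up after removal, the article should be brought into line with it.

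**What to change.** 1. In {22}, add death (woman, fetus or newborn), hospital admission or its prolongation, and congenital anomaly to the SAE criteria, and state that events in the fetus and newborn count.
2. Reconcile {11b} and {22}. Whatever is decided about study drug, SAEs and the pregnancy and newborn outcome should still be collected and reported for every randomised woman who has not withdrawn consent, without a filter on suspected cause.
3. Reconcile {30} with the day-28 outcome in {12}, {13}, {18a} and the Study outcomes text, so that the end of the safety window is clear.
4. As a lesser matter, state how events reach the DSMB, since one criterion depends on its decision.

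The cost is a short amendment and revised SAE form text, a few more reports, and some outcome contacts at delivery and day 28 for removed women. Trial status says that recruitment is complete but last visits were still pending at submission. New collection can therefore reach only the remaining follow-up, but events already recorded as AEs or outcomes can be reclassified against the wider list.
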